#### Secondary analyses

The outcome of superficial-incisional, deep-incisional, organ/space, and/or complex SSIs will be analyzed similarly to the primary outcome. The rate of signals per 100 procedures performed will be compared between optimized SPC and traditional surveillance methods using a similar approach as for the primary outcome. Sensitivity and positive predictive value to identify important increases in SSI rates (defined as signals that lead to investigations) will be compared between optimized SPC and traditional surveillance methods using chi-square or Fisher’s exact test, as appropriate. For a subset of true positive signals that are generated by both methods, average time between signals will be summarized, and a proportion of true positive signals in which optimized SPC methods identified the signal first will be estimated. The remaining secondary outcomes will be analyzed using summary statistics only.

Full details of the statistical analysis will be specified in the statistical analysis plan prior to the study database lock.

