### Intervention description {11a}

Data entered locally by infection preventionists at DICON hospitals are transmitted to the DICON Surgical Database per routine practices. Data submitted to the DICON Surgical Database will undergo scheduled weekly analysis by optimized SPC methods. If a signal is generated, study personnel in DICON will be notified to adjudicate the signal and determine if further action is required.

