### Outcomes {12}

Primary endpoint (domain: healthcare-associated infection):
Specific measurement – SSI rate, calculated as the number of SSIs per 100 proceduresSpecific metric – Differences in the rates of SSI between the intervention compared to traditional surveillance and feedback alone
SSIs will be defined using standard NHSN definitions
i.DICON personnel train local infection preventionists about how to use and interpret SSI definitions. Thus, standard definitions and methods will be used at all study hospitalsCluster-level risk adjustment will be performed using median surgical volume [25] and median NHSN Risk Index (an operation- and patient-specific risk score that predicts SSI) [26, 27] per clusterMethod of aggregation – Mean rates will be summarized for each cluster for each 3-month study “step”

Secondary endpoints:
Several secondary outcomes will be compared between clusters receiving intervention and clusters receiving traditional surveillance and feedback
Stratified analysis of primary outcome – SSI rates stratified by type of SSI (superficial-incisional, deep-incisional, or organ/space).Descriptive outcomes
◦ Description of and difference in number and type of signals◦ Difference in number of investigations of increased rates of SSI◦ Total number and differences in proportion of signals that led to investigations◦ Proportion of SSIs determined to be potentially preventable, based on preventability score◦ Timing of signals

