**Fig. 2 Fig2:**
[figure not shown]
Schematic for stepped wedge design for the Early Recognition and Response to Increases in Surgical Site Infection (Early 2RIS) Trial. Gray = control, during which hospitals will receive traditional SSI surveillance, including biannual data reports. Any signals identified in biannual reports or detected by local personnel will undergo further investigation. White = intervention, during which hospital clusters will receive feedback from traditional surveillance and signals generated by applying optimized SPC methods to SSI surveillance data

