## Assignment of interventions: blinding

### Who will be blinded {17a}

SSI signals prospectively identified using optimized SPC methods during the intervention period will undergo blinded review to ensure that signal adjudication occurs without knowledge of which hospital cluster generated the signal. Following review, the study coordinator will unblind the signal, and, if the hospital cluster is randomized to intervention, the study team will proceed with the actions required to appropriately respond to the identified increase in SSIs. If the hospital cluster is a control cluster, then the study coordinator will document the signal, but no further action will be taken.

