## Data collection and management

### Plans for assessment and collection of outcomes {18a}

Routine data on surgical procedures and SSIs will be collected via a standardized limited dataset, per routine DICON practices (Table 2) [28]. No identifiable patient or surgeon data are transmitted to the DICON Surgical Database.

**Table 2 Tab2:** Variables in the DICON Surgical database

All surgical patients	Hospital
	Type of procedure
	Patient identifier
	Date of procedure
	Age
	Sex
	Surgeon identifier
	Start/stop times
	ASA score
	Wound class
	Risk index
	SSI (yes/no)
Patients with Infection	Date of infection
	Type of SSI
	Location at diagnosis
	Organism

When a signal is identified, data will be collected on the rationale for signal adjudication (action vs. no action). If a signal requires action, additional data will be collected for further investigation, per routine protocol.

The majority of data collection will occur through methods already developed and utilized by study hospitals. In brief, each hospital routinely submits limited datasets to the DICON Surgical Surveillance Database, including all variables listed in Table 2. Data definitions and data collection methods are standardized across DICON hospitals. Following signal adjudication, additional data will be collected in a REDCap database to document actions and rationale.

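### A true positive is a signal that was investigated, but investigation rules differ by method and phase, so the PPV comparison partly measures handling and not accuracy

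*Protocol article*

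**What the plan says.** The Secondary objectives ask for true positives, false positives, PPV, sensitivity and specificity of each method, under the same objective as the proportion of signals investigated. Outcomes {12} lists "Total number and differences in proportion of signals that led to investigations". The Secondary analyses section gives the reference standard: "positive predictive value to identify important increases in SSI rates (defined as signals that lead to investigations) will be compared". It also names the test: these measures "will be compared between optimized SPC and traditional surveillance methods using chi-square or Fisher’s exact test, as appropriate".

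Four places say what happens to a signal:

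- **Traditional, control period** (Fig. 2 legend, Participant timeline {13}): "Any signals identified in biannual reports or detected by local personnel will undergo further investigation".
- **SPC, any cluster** (Intervention description {11a}): "study personnel in DICON will be notified to adjudicate the signal and determine if further action is required". Under Who will be blinded {17a}, SPC signals "will undergo blinded review to ensure that signal adjudication occurs without knowledge of which hospital cluster generated the signal".
- **SPC, control cluster, after unblinding** ({17a}): "If the hospital cluster is a control cluster, then the study coordinator will document the signal, but no further action will be taken".
- **Signals in general** (Plans for assessment and collection of outcomes {18a}): "data will be collected on the rationale for signal adjudication (action vs. no action", with further investigation if action is required.

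**The concern.** PPV is true positives divided by all signals. When a true positive is any signal that was investigated, PPV equals the proportion investigated, and a false positive is a signal nobody followed up. That works as a yardstick only if the decision to investigate is made in the same way for both methods. Here it is not: the control-period rule for traditional signals has no filter, the rule for SPC signals in intervention clusters has one, and the rule for SPC signals in control clusters stops follow-up whatever the reviewers concluded.

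At stake is a named secondary objective. A lower PPV for SPC could be reported as weaker predictive value when some or all of the gap comes from how signals were processed. The point concerns only how flagged signals are classified. Increases that neither method flags are a separate matter.

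**Working it through.** The article gives no PPV, signal count or power for this comparison, so there is no figure to reproduce. The check applies the stated rules to each stream of signals.

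**Step 1. PPV by stream.** PPV = investigated signals / all signals. Let *a* be the share of intervention-cluster SPC signals adjudicated to action.

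| Stream | Rule | PPV |
|---|---|---|
| Traditional, control period | all investigated (Fig. 2 legend) | 100%, whatever the data |
| SPC, control cluster | no action ({17a}) | 0% through SPC, whatever the data |
| SPC, intervention cluster | adjudicated first ({11a}, {17a}, {18a}) | *a*, observed, from 0 to 100% |

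Against a fixed 100%, SPC ties only if *a* = 100%. Otherwise it is lower, and it can never be higher.

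**Step 2. Pooled SPC PPV if control-phase signals are counted.** Inputs from the Abstract: 105 clusters, 8–9 crossing every 3 months over 3 years, hence 12 steps and 105/12 = 8.75 per step. Assume equal waves that switch at the start of each step.

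- Intervention cluster-quarters: 8.75 × (1 + 2 + … + 12) = 8.75 × 78 = 682.5.
- All post-baseline cluster-quarters: 105 × 12 = 1,260.
- Control cluster-quarters: 1,260 − 682.5 = 577.5 (46%).

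Assume equal signal rates in both phases, and let *c* be the share of control-cluster SPC signals that coincide with an investigated traditional signal and are credited as true positives:

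Pooled PPV = (682.5*a* + 577.5*c*) / 1,260.

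- *a* = 100%, *c* = 0: 682.5/1,260 = 54.2%.
- *a* = 50%, *c* = 0: 341.25/1,260 = 27.1%.
- *a* = 100%, *c* = 20% (assumed, to show the effect of overlap): (682.5 + 115.5)/1,260 = 63.3%.

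**Step 3. Intervention-only reading.** If only intervention-cluster SPC signals count, SPC PPV is *a* and Step 2 falls away. Whether Fisher's exact test then finds a difference from a fixed 100% depends on *a* and on the counts. With 100 SPC signals and an assumed number of traditional signals, all investigated, the p-values are:

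| Traditional signals | *a* = 100% | 90% | 80% | 70% | 50% |
|---|---|---|---|---|---|
| 10 | 1.00 | 0.59 | 0.20 | 0.059 | 0.002 |
| 20 | 1.00 | 0.21 | 0.024 | 0.003 | <0.001 |
| 50 | 1.00 | 0.031 | <0.001 | <0.001 | <0.001 |

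**Step 4. What a common standard might show.** Section {6b} gives the SPC charts sensitivity 0.90 and specificity 0.67 (training), and 0.88 and 0.75 (validation). With PPV = Se·p / [Se·p + (1 − Sp)(1 − p)] and an assumed prevalence p of true increases, PPV is 0.23–0.28 at 10%, 0.41–0.47 at 20% and 0.73–0.78 at 50%. So SPC may well have a modest PPV in truth. The article gives no specificity for traditional surveillance, so its PPV on the same standard cannot be computed. The planned comparison would not supply it for control periods either, because the rule sets it at 100%.

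**The case against.** The strongest reply has five parts.

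1. A reader might infer that the whole comparison is settled by rule and that data play no part. The documents do not support that. SPC signals in intervention clusters are investigated or not after blinded review, so that share, the size of the gap and the p-value are partly data.

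2. A reader might infer that every SPC signal in a control cluster must be a false positive and that 54% is a firm ceiling. Section {17a} says only that no further action follows from the SPC signal. The same increase could be picked up by a biannual report or local staff and investigated, and the Secondary analyses section foresees true positives flagged by both methods. Nor does any section say that control-phase SPC signals enter the denominator; both methods run in intervention clusters, so a comparison within intervention time is an equally available reading. A still lower ceiling, from assuming fewer signals after crossover, has no basis either: the only planned reduction in the article is in the SSI rate, and Chart B compares a hospital with its own recent rates.

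3. The 100% rests on a figure legend describing control periods. Section {18a} speaks of adjudicating a signal without limiting this to SPC, and the objectives treat the investigated proportion as something to estimate for both methods. This stands as a reason to reconcile the two places. It does not remove the legend's rule.

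4. The charts are deliberately tuned for screening ({6b}), and several of these outcomes are headed descriptive in {12}. Both are true. But a tested comparison of PPV is stated, and an expected low SPC PPV makes it more important that both methods face the same standard.

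5. Details may be left to the SAP. That covers the choice of denominator. It does not cover the reference standard, which the article itself fixes.

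**Conclusion.** The concern holds in limited form. By the stated rules, control-period traditional signals have a PPV of 100% and SPC can only tie or fall below it, so the PPV and false-positive comparison mixes handling with accuracy and the mixture works against SPC. The one component the data determine is the share of intervention-cluster SPC signals adjudicated to action.

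The size depends on the reading. Pooled SPC PPV is capped near 54% only if control-phase SPC signals are counted, signal rates are equal in both phases, no such signal overlaps an investigated traditional one, and clusters cross in equal waves at the start of each step. Under an intervention-only reading there is no such cap, and the gap is 100% minus the observed share. It does not follow that the trial is bound to report much poorer predictive value for SPC. The 100% itself assumes that the Fig. 2 legend, and not the general wording of {18a}, governs traditional signals. The primary SSI-rate analysis is not touched. The definition should be corrected before these secondary results are analysed.

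**What to change.** - In the Secondary objectives, Outcomes {12} and the Secondary analyses section, define true and false positives by the action/no-action adjudication verdict recorded before unblinding, and not by whether an investigation followed. For SPC signals the plan already collects this verdict in both phases.
- Put traditional signals through the same adjudication form, with cluster identity masked where feasible. Signals raised by local staff come from people who know the cluster, so masking can apply only to the adjudicators; say where it was not possible.
- State which phases' signals enter the denominator for each method, and report PPV by phase.
- Reconcile the Fig. 2 legend with {18a} on whether traditional signals are adjudicated before investigation.
- Keep the proportion investigated as a process description only, not as a comparison of accuracy.

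This changes definitions and analysis wording and leaves the response to signals in either arm as it is. The cost is a small amount of extra adjudication work for the traditional signals. It can be settled in the SAP, which the article says will be completed before database lock.

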**Fig. 1 Fig1:**
[figure not shown]
Example SPC charts used for SSI surveillance in the Early 2 RIS Trial; Chart A (top) is a moving average (MA) chart using DICON baseline rates and Chart B (bottom) is a moving average (MA) chart using local hospital rates

Importantly, SPC surveillance should be viewed as an adjunct to traditional surveillance. That is, traditional surveillance will still be performed in both arms to identify and document SSIs as they occur in study hospitals. In the intervention arm, optimized SPC surveillance will be applied to SSI surveillance data after traditional surveillance is performed to rapidly identify if the data entered and new SSI rates are not in line with expected rates (a “signal”).

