## Assignment of interventions: allocation

### Sequence generation {16a}

Randomization and allocation sequence will be performed using computer-generated random numbers. However, at most, one cluster per hospital will be changed to the intervention during any individual step; all remaining clusters will continue to receive standard, traditional surveillance and feedback. Once randomized to intervention, clusters will receive surveillance from both optimized SPC and standard methods for the remainder of the study. At the last step, the remaining cluster within each hospital (if any) will begin the intervention.

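### Sensitivity and PPV of two surveillance methods that run on the same clusters are to be compared with tests for independent samples; the p-values are not valid, and the direction of error depends on the reference set

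*Protocol article*

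**What the plan says.** The test is fixed in Statistical methods {20a}, Secondary analyses. The target is defined there: "Sensitivity and positive predictive value to identify important increases in SSI rates (defined as signals that lead to investigations". The two measures "will be compared between optimized SPC and traditional surveillance methods using chi-square or Fisher’s exact test, as appropriate". Pairing and clustering are not mentioned for this comparison. The next sentence but one turns to timing and begins: "For a subset of true positive signals that are generated by both methods". The plan therefore expects the two methods to flag some of the same increases.

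Other sections describe how the methods overlap:

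- Explanation for the choice of comparators {6b}, text after Fig. 1: "traditional surveillance will still be performed in both arms to identify and document SSIs as they occur in study hospitals", and in the intervention arm "optimized SPC surveillance will be applied to SSI surveillance data after traditional surveillance is performed".
- Sequence generation {16a}: after crossover, "clusters will receive surveillance from both optimized SPC and standard methods for the remainder of the study".
- Who will be blinded {17a}: SPC also runs in control clusters. "If the hospital cluster is a control cluster, then the study coordinator will document the signal, but no further action will be taken".

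By contrast, the Primary analyses paragraph models correlation within clusters over time and between clusters of one hospital, and the signal rate per 100 procedures is to be handled in a similar way. Only sensitivity and PPV are given tests without it.

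**The concern.** Pearson's chi-square and Fisher's exact test compare two separate groups of independent observations. Here the two sensitivities share one denominator, the set of important increases, and each increase carries two results, one per method. An unpaired test sets the covariance between them to zero.

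For PPV the denominators are each method's own signals. These sets overlap in part and are grouped within clusters and hospitals. Charts A and B use 12-month and 6-month moving averages, so successive signals from one cluster draw on overlapping data.

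Detection accuracy is a stated secondary objective and part of the rationale for SPC. An invalid test could support a difference that the data do not show, or miss one that they do.

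**Working it through.** The article gives no sample size, power or p-value for this comparison, so there is no figure to reproduce. The numbers of increases, the overlap and the correlations below are assumptions. The level is two-sided 5%.

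**Sensitivity, every counted increase flagged by at least one method.** The definition as signals that lead to investigations implies this. Let a be the share flagged by both methods. With truly equal methods, the share flagged by each method alone is b = (1 - a)/2, the sensitivity is p = a + b, and no increase is missed by both.

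- Variance of the difference assumed by the unpaired test: 2p(1 - p)/n
- True paired variance: 2b/n
- True size: 2 × [1 - Φ(1.96 × √(p(1 - p)/b))]

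| a | p | 2p(1 - p) | 2b | True size |
|---|---|---|---|---|
| 0 | 0.5 | 0.50 | 1.00 | 16.6% |
| 0.2 | 0.6 | 0.48 | 0.80 | 12.9% |
| 0.4 | 0.7 | 0.42 | 0.60 | 10.1% |
| 0.6 | 0.8 | 0.32 | 0.40 | 8.0% |

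Simulation with 50, 100 and 200 increases agrees: about 8% at sensitivity 0.8 and 10% at 0.7, with 18-20% at 0.5. Fisher's test gave about 5% to 14.5%. McNemar's test stayed at 4.3% to 6.4% in all null scenarios. Zero overlap is a limiting case, since the plan itself expects some.

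**Sensitivity, increases missed by both methods also counted.** With correlation rho between the methods, the true size is 2 × [1 - Φ(1.96/√(1 - rho))].

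- rho = 0.3: 1.96/√0.7 = 2.34, size 1.9%
- rho = 0.6: 1.96/√0.4 = 3.10, size 0.2%

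The cost is power. With 50 increases, sensitivities 0.80 and 0.65 and rho = 0.3, simulated power is 0.37 for Pearson and 0.50 for McNemar. The two errors cancel when the share missed by both equals (1 - p)²: 9% at p = 0.7, 4% at p = 0.8.

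**Two illustrative tables.**

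| Both | SPC only | Traditional only | Neither | Pearson | Fisher | McNemar | Exact McNemar |
|---|---|---|---|---|---|---|---|
| 30 | 20 | 10 | 0 | 0.035 | 0.057 | 0.068 | 0.099 |
| 50 | 14 | 4 | 32 | 0.151 | 0.196 | 0.018 | 0.031 |

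In the first, Pearson is χ² = 4.44 and McNemar is (20 - 10)²/30 = 3.33. In the second, Pearson is 2.07 and McNemar is (14 - 4)²/18 = 5.56. The Pearson verdict is wrong in opposite directions.

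**PPV.** Assume 105 clusters, 2 to 10 signals per cluster per method, and an intraclass correlation (ICC) of 0.1 to 0.2. If cluster effects are fully shared by the methods, the simulated size is about 5%. If they are specific to each method, it is about 9-18%. As a check, with m signals per cluster the design effect is 1 + (m - 1) × ICC and the size is 2 × [1 - Φ(1.96/√design effect)].

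- m = 5, ICC 0.1: design effect 1.4, size 9.8%
- m = 5, ICC 0.2: design effect 1.8, size 14.4%
- m = 6, ICC 0.2: design effect 2.0, size 16.6%

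If every cluster sat at one end of the range, the formula would give 6.2% (m = 2, ICC 0.1, design effect 1.1) and 24% (m = 10, ICC 0.2, design effect 2.8). The 9-18% thus describes counts in the middle of the range.

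**Which increases can be paired.** A control-phase SPC signal is documented and leads to no action, so under the stated definition it cannot be an SPC true positive on its own. The Fig. 2 caption sends control-phase signals from biannual reports or local personnel to investigation. Read literally, an increase found by SPC alone cannot be counted in control phases, and a paired test over all phases would be biased against SPC.

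**The case against.** The strongest reply is that the direction of error is not established. A reader might infer from the definition that the type I error is simply inflated and the intervals too narrow. The article does not support so flat a claim. The Fig. 2 caption adds increases noticed by local personnel as a further route to investigation and does not say whether they are credited to traditional surveillance. If they are not, some counted increases were missed by both methods, and the test may be about right or conservative. This stands.

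A reader might likewise infer that the PPV p-values must be wrong. Both methods read the same SSI data, so cluster effects are probably shared in part, and the error may be small. This also stands.

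Outcomes {12} can be read as comparing intervention clusters with control clusters, in which case McNemar's test would not apply. Independence still fails, because each cluster contributes to both phases and signals recur within clusters and hospitals.

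The practical effect may be limited. The article cites sensitivities of 0.88-0.90 for SPC and 33-65% for traditional surveillance. At 0.88 against 0.65 with no increase missed by both, chi-square and McNemar disagreed on significance in 7% of simulated trials with 50 increases, 2.6% with 100 and 0.1% with 200. That bears on severity, not on correctness.

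Finally, the phrase on appropriateness and the promised analysis plan leave room for refinement. But the tests are named, and pairing chi-square with Fisher's test is the usual wording for unpaired tables.

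**Conclusion.** The point holds: the named tests do not fit the design, and the p-values and intervals for sensitivity and PPV are not valid as planned. For sensitivity, the true size is about 8-17% if every counted increase was flagged by at least one method. It is below 5%, with lost power, if increases missed by both are counted and the methods agree positively. For PPV, the error runs from about none to 9-18%. The sensitivity figures assume equal methods and ignore clustering; the PPV figures rest on assumed signal counts and ICCs. A claim of inflation in one direction only is not supported. The matter concerns secondary outcomes, should be corrected, and leaves the primary SSI-rate analysis untouched.

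**What to change.** Replace the chi-square and Fisher sentence as follows.

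1. **Sensitivity.** Compare the methods on one common set of increases by logistic GEE, with method as a within-increase factor and clustering on hospital, or by McNemar's test with a cluster-adjusted variance. Plain McNemar would still ignore hospital clustering. Restrict the set to intervention-phase cluster-time, where signals from both methods can lead to investigation. If control phases are included, use the blinded adjudication verdict as the reference instead of an actual investigation. The article describes blinded review only for SPC signals, so that option needs the same verdict for traditional signals.
2. **PPV.** Fit a logistic GEE of the signal verdict on method, with hospital-clustered robust variance.
3. **Reference set.** State whether increases noticed only by local personnel count, and to which method they are credited. Report differences with confidence intervals.

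The cost is a few sentences before database lock and slightly more analysis work. No new data are needed if sensitivity is confined to intervention-phase time. Intervals may become wider or narrower.

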### Secondary objectives

To determine if hospital clusters randomized to SSI surveillance with optimized SPC methods and feedback collectively have lower rates of superficial-incisional, deep-incisional, organ/space, and/or complex SSI compared to hospital clusters randomized to traditional SSI surveillance methods and feedback.To determine and compare the number of signals identified using optimized SPC methods and traditional surveillance methods over the 3-year post-baseline period.
Descriptive – overall numbers; then summarize per cluster per monthFor comparison – develop standardized rate, likely number of signals per 100 procedures performedTo estimate and compare the proportion of signals that led to investigations using optimized SPC methods versus traditional surveillance methods, including the number of true positive signals, false positive signals, positive predictive value, sensitivity, and specificity of each method.To summarize the preventability score for SSIs reviewed during the study and compare between treatment arms.To compare the timing of true positive signal identification between the two surveillance strategies.
Average time between signalsProportion of true positive signals in which optimized SPC methods found the signal first.

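### Signal timing is summarised only for true positives flagged by both methods, a set that is narrower than the objective and that action on SPC signals can itself change

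*Protocol article*

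**What the plan says.** The secondary objective is "To compare the timing of true positive signal identification between the two surveillance strategies". Under it the article lists two measures: the average time between signals, and the proportion of true positive signals that SPC found first. It does not restrict either to signals raised by both methods.

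The Secondary analyses section narrows this: "For a subset of true positive signals that are generated by both methods, average time between signals will be summarized", continuing "and a proportion of true positive signals in which optimized SPC methods identified the signal first will be estimated". The second clause shares the sentence and its opening condition, although it could be read on its own. No trial phase is named. In the preceding sentence, on sensitivity and positive predictive value, important increases are "defined as signals that lead to investigations".

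Four other places matter:
- Intervention description {11a}: "Data submitted to the DICON Surgical Database will undergo scheduled weekly analysis by optimized SPC methods".
- Who will be blinded {17a}: after blinded review of an SPC signal from an intervention cluster, "the study team will proceed with the actions required to appropriately respond to the identified increase in SSIs". For the other clusters: "If the hospital cluster is a control cluster, then the study coordinator will document the signal, but no further action will be taken".
- Fig. 2 legend: traditional signals come from biannual reports or local personnel and are investigated. Sequence generation {16a} adds that both forms of surveillance continue after crossover.
- Plans for assessment and collection of outcomes {18a}: when a signal is identified, "data will be collected on the rationale for signal adjudication (action vs. no action").

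**The concern.** An increase enters the timing set only if the second method also signals. In intervention clusters that second event comes after the SPC signal and after any action on it. If the action works, traditional surveillance may never signal, and an increase that SPC found first leaves the set. The increases that stay are those where traditional surveillance signalled soon after SPC or before it, or where action came too late or failed. The set is therefore shaped by the intervention, and the more effective the response, the more SPC-first increases are lost.

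There is a second gap. If a true positive is a signal that led to an investigation, an SPC-only signal in a control cluster can never qualify, because nothing further is done about it. Yet control clusters are where SPC can be timed against traditional surveillance without SPC-triggered action.

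At stake is the trial's evidence that SPC detects increases earlier, which is the rationale the article gives for the method.

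**Working it through.** The documents give no figure for this analysis, so there is none to reproduce. Two illustrations show the possible size.

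**1. Overlap of the two methods, before any action**

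Explanation for the choice of comparators {6b} gives SPC sensitivity *s* = 0.88 to 0.90 and traditional sensitivity *t* = 0.33 to 0.65. Applying *t* to rate increases is an assumption: it may describe detection of individual infections, although the article sets it against the SPC figures.

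- Share of SPC-detected increases not flagged traditionally, under independence: *s*(1 − *t*)/*s* = 1 − *t*, so 1 − 0.65 = 35% to 1 − 0.33 = 67%.
- Over every possible dependence, the both-flagged probability lies between max(0, *s* + *t* − 1) and min(*s*, *t*). The smallest share is 1 − 0.65/0.88 = 26%. The largest is 1 − (0.88 + 0.33 − 1)/0.88 = 1 − 0.21/0.88 = 76%.
- Suppose 70% of both-flagged increases were SPC-first. Over increases flagged by either method, SPC-first = (0.7 × both + SPC-only)/any.
  - *s* = 0.88, *t* = 0.65: (0.7 × 0.572 + 0.308)/(0.572 + 0.308 + 0.078) = 0.708/0.958 = 74%.
  - *s* = 0.90, *t* = 0.33: (0.7 × 0.297 + 0.603)/(0.297 + 0.603 + 0.033) = 0.811/0.933 = 87%.
- The restriction alone does not always lower the proportion. With 90% in place of 70%, the same formula gives 86% and 93%.

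**2. Effect of acting on SPC signals**

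This is a simulation of 400,000 increases per scenario. Every input is an assumption:
- onset uniform in a six-month report cycle;
- exponential duration, mean 6 or 12 months;
- exponential SPC delay, mean 1.5 or 3 months;
- SPC sensitivity 0.9;
- a traditional flag at a biannual report when at least 3 raised months fall in that half-year;
- resolution one month after an SPC signal that is acted on.

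Each cell reads: no action → action.

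| Mean duration / SPC delay (months) | SPC-detected, outside both-flagged set | SPC-first, both-flagged | Mean SPC lead, both-flagged (months) | SPC-first, either-flagged |
|---|---|---|---|---|
| 6 / 1.5 | 33.6% → 87.7% | 97.5% → 86.7% | 4.37 → 1.66 | 90.3% → 90.3% |
| 6 / 3 | 27.0% → 73.1% | 90.3% → 73.9% | 3.44 → 0.96 | 79.1% → 79.2% |
| 12 / 1.5 | 18.4% → 84.8% | 97.2% → 84.4% | 4.45 → 1.56 | 88.8% → 88.7% |
| 12 / 3 | 13.9% → 66.4% | 87.8% → 69.0% | 3.29 → 0.62 | 77.3% → 77.3% |

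Action lowered SPC-first in the both-flagged set by 11 to 19 percentage points and mean lead by 2.5 to 2.9 months, in the same direction in all four scenarios. The either-flagged proportion did not move. That is close to structural: an increase SPC found first stays SPC-first whether or not the other method signals later.

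**3. How much control-phase exposure exists**

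If 105 clusters cross over evenly in 12 steps (8.75 per step, at the start of each step), there are 105 × 12 = 1,260 post-baseline cluster-steps. Of these, 8.75 × (1 + 2 + … + 12) = 8.75 × 78 = 682.5 are intervention and 577.5 (46%) are control. This is a share of exposure, not of signals.

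**The case against.** The strongest reply is that a time between two signals exists only when both occur, so for that measure the restriction follows from the definition. The SPC-first clause can be read without it, the outcome is only summarised, and full details are deferred to the statistical analysis plan, which is not shown. All of this stands. It does not settle the point, because the protocol itself names a subset and the objective names a wider denominator.

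The size of the effect is also open. No section says how quickly action ends an increase, and a biannual report may still count infections that occurred before resolution. The simulation allows for the latter by counting raised months across the half-year, but its durations, delays and resolution time are assumed.

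Counting every increase missed by the other method as a first detection mixes sensitivity with timing. That is a fair objection, and the three counts proposed in the fix answer it.

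A reader might infer three stronger things that the documents do not support:
- *That objective and analysis contradict each other.* The analysis is narrower and ambiguous, not incompatible.
- *That control-phase data are excluded.* No phase is named, and control-phase traditional signals are investigated, so increases flagged by both methods there can enter. Only SPC-only control signals are lost, and only if the investigation-based definition carries over from the preceding sentence.
- *That weekly against biannual looks make SPC first almost by schedule.* The charts use 6- and 12-month moving averages, local personnel can detect increases at any time, and frequent looks are part of the strategy under test. Such an argument would also point the opposite way from the bias described here.

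**Conclusion.** The point holds in a limited form. The timing summary, and on its natural reading the SPC-first proportion, are confined to increases flagged by both methods. That is narrower than the objective, and in intervention clusters membership of the set can be altered by acting on SPC signals.

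The selection from acting on SPC signals works against SPC: it can understate both lead time and the SPC-first proportion. The restriction alone, without that action, can move SPC-first either way. About one third to two thirds of SPC-detected increases could fall outside the set before any action, if the quoted sensitivities apply to rate increases and the methods are independent. The further loss from action is plausible, and its direction was consistent across the scenarios, but its size depends on assumed inputs.

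It is worth correcting because the control-phase SPC signals are already reviewed and recorded. It concerns a descriptive secondary outcome and does not affect the primary analysis.

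**What to change.** - Reconcile Secondary objectives with Secondary analyses, stating the denominator for each timing measure.
- Report timing separately by phase. Make control-phase cluster-steps the main comparison, since SPC signals there are adjudicated but not acted on.
- Define true positives by the blinded adjudication result (action or no action) rather than by whether an investigation followed, and apply the same standard to traditional signals.
- Use increases flagged by either method as the SPC-first denominator. Show SPC-only, traditional-only and both-flagged counts, so that sensitivity and timing can be told apart.
- Keep paired lead time as a description of both-flagged increases. Add a supporting summary in which a missing second signal is treated as censored.

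The cost is more than wording. Signals from the two methods must be matched into episodes, and a little more analysis is needed. The article describes blinded review for SPC signals only, so applying the same standard to traditional signals may need some added adjudication. The control-phase SPC signals and the adjudication rationale are already planned to be recorded.
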